# Design of a randomised controlled hybrid trial of nintedanib in patients with progressive myositis-associated interstitial lung disease

**DOI:** 10.1186/s12890-024-03314-0

**Published:** 2024-10-30

**Keywords:** Clinical trial, Connective tissue diseases, Dermatomyositis, Polymyositis, Interstitial fibrosis, Pulmonary fibrosis

## Abstract

**Background:**

The Myositis Interstitial Lung Disease Nintedanib Trial (MINT) is a hybrid trial, which is enrolling patients both at local sites and remotely via a decentralised site. The trial will investigate the efficacy and safety of nintedanib in patients with progressive myositis-associated interstitial lung disease (MA-ILD).

**Methods/Design:**

MINT is an exploratory, prospective randomised placebo-controlled trial. Eligible patients will have myositis and evidence of fibrosing ILD on high-resolution computed tomography (HRCT), be taking standard of care medications for myositis, and meet criteria for ILD progression within the prior 24 months based on decline in FVC, worsened fibrosis on HRCT, and/or worsened dyspnoea. Patients will be randomised 1:1 to receive nintedanib 150 mg twice daily or placebo for 12 weeks then open-label nintedanib for 12 weeks. Patients will be enrolled at local sites and a decentralised site. Most study visits will be completed remotely using telemedicine or digital health technologies. The primary endpoint is the change in Living with Pulmonary Fibrosis (L-PF) questionnaire dyspnoea domain score at week 12. Other endpoints include changes in other L-PF questionnaire domains, lung function, imaging, and physical activity, and assessment of adverse events. Data collected using remote versus clinic enrolment, and using home versus clinic spirometry, will be compared.

**Discussion:**

MINT is an innovative, hybrid trial that will evaluate the effects of nintedanib on symptoms, quality of life, and ILD progression in patients with progressive MA-ILD and provide valuable information on the utility of decentralised recruitment and remote data collection in clinical trials.

**Trial registration:**

Clinicaltrials.gov NCT05799755 (date of registration: 05/04/2023).

**Supplementary Information:**

The online version contains supplementary material available at 10.1186/s12890-024-03314-0.

## Background

Myositis comprises a group of autoimmune disorders characterised by weakness and inflammation of the muscles [1]. A proportion of patients with myositis develops interstitial lung disease (ILD) [2–5], which is associated with cough, dyspnoea, fatigue, reduced quality of life, and premature mortality [6–8]. Patients with anti-synthetase antibodies are at greater risk of developing ILD than patients with other myositis autoantibodies [8]. In clinical practice, myositis-associated ILD (MA-ILD) is usually treated with glucocorticoids and/or other immunosuppressive therapies [9–11]. A guideline issued by the American College of Rheumatology and American College of Chest Physicians conditionally recommended mycophenolate, azathioprine, rituximab, cyclophosphamide, Janus kinase inhibitors, calcineurin inhibitors, or short-term glucocorticoids as first-line treatment options for idiopathic inflammatory myopathies including MA-ILD [12].

Despite treatment, some patients with MA-ILD develop progressive pulmonary fibrosis characterised by increasing radiological fibrosis, decline in lung function, and premature mortality [3, 4, 13–16]. Nintedanib is a tyrosine kinase inhibitor that inhibits processes fundamental to the progression of pulmonary fibrosis [17, 18]. In the recent guideline issued by the American College of Rheumatology and American College of Chest Physicians, nintedanib received a conditional recommendation for use in patients whose MA-ILD had progressed despite first-line treatment [12]. A guideline issued by international respiratory societies for the treatment of progressive pulmonary fibrosis in patients with diagnoses other than idiopathic pulmonary fibrosis (IPF) also provided a conditional recommendation for the use of nintedanib in patients who have “failed standard management” [19]. In the randomised, placebo-controlled INBUILD trial in patients with progressive pulmonary fibrosis, nintedanib reduced the decline in forced vital capacity (FVC) over 52 weeks by 57%, with an adverse event profile characterised mainly by gastrointestinal events [20–22], similar findings to those previously observed in patients with IPF [23] and systemic sclerosis-associated ILD [24]. The INBUILD trial was not powered to study patients with specific diagnoses, but no heterogeneity was detected in the effect of nintedanib across subgroups by diagnosis [25, 26], or based on the introduction of immunomodulatory therapies during the trial [27]. Data collected using the Living with Pulmonary Fibrosis (L-PF) questionnaire suggested that nintedanib lessened the symptoms and impact of ILD [28]. However, nintedanib is not commonly used in patients with MA-ILD, likely due to a lack of clinical data supporting its safety and efficacy in this specific population; only two patients in the INBUILD trial had a diagnosis of polymyositis‐associated ILD or antisynthetase syndrome noted on the case report form [26].

The Myositis Interstitial Lung Disease Nintedanib Trial (MINT) was designed to evaluate the effects of nintedanib in patients with progressive MA-ILD taking standard of care therapy. MINT has a novel hybrid design that includes both traditional clinical sites and a decentralised site, and most study visits will be conducted remotely. This will enable evaluation of the utility of decentralised recruitment and remote data collection, and of novel measures such as physical activity monitors and home spirometry. In this manuscript, we describe the key design elements of this innovative trial.

## Methods/design

### Study design and participants

MINT is an exploratory, multi-centre, prospective, randomised, double blind, placebo-controlled trial. Eligible patients will be randomised 1:1 to receive nintedanib 150 mg twice daily (bid) or placebo stratified by local vs decentralised site and by use of immunosuppressive therapy (mycophenolate mofetil vs others). Patients will receive blinded treatment for 12 weeks, after which all patients will receive open-label nintedanib for 12 weeks (Fig. 1). Treatment interruptions for ≤ 4 weeks and dose reductions to 100 mg bid will be allowed to manage adverse events. Specific recommendations will be provided to the investigators for the management of diarrhoea and hepatic enzyme elevations (Additional file 1). Patients who prematurely discontinue trial medication will be asked to complete all scheduled visits.

**Fig. 1 Fig1:**
[figure not shown]
Design of MINT

### Recruitment, consent, and screening

The trial will use two methods of recruitment: at local sites and decentralised (Fig. 2). Patients will be recruited conventionally at 15 sites through clinic referrals, local registries, advertisements on flyers and websites, and mailings/emails to local physicians. For these patients, pre-screening and consent can be conducted at the local site, via telemedicine, or a combination of both. In addition, patients from anywhere in the USA will be recruited using a decentralised approach, managed through the University of Pittsburgh. Patients and physicians will be approached using a number of methods including via social media and patient/physician organisations (Fig. 3). Patients will be directed to a website providing detailed information about the trial, a consent form, and a link to a preliminary pre-screening questionnaire. After completing this questionnaire, they will be directed for pre-screening consent and release of medical information. Approval will be obtained from the patient’s treating physician. Medical records will be reviewed by a trial investigator. Consent for screening will be obtained via telemedicine and a screening visit will then be arranged.

**Fig. 2 Fig2:**
[figure not shown]
Flow through decentralised recruitment and data collection in MINT

**Fig. 3 Fig3:**
[figure not shown]
Methods used to approach patients and physicians for decentralised recruitment to MINT

For all patients, screening will be conducted via telemedicine and using digital health technologies at the patient’s home, except for high-resolution computed tomography (HRCT) scans (if one has not been done in the prior 3 months) and clinic pulmonary function tests (PFTs), which will be performed at a centre near the patient’s home. For the blood sampling needed for laboratory assessments, a research nurse will visit the patient’s home. Patients recruited via a local site will also have the option to have some screening assessments at the local site.

The trial protocol was approved by an ethics review board at the University of Pittsburgh School of Medicine (STUDY22090057). The trial will be conducted in accordance with the International Conference on Harmonisation Guideline for Good Clinical Practice, Declaration of Helsinki principles, and local regulatory, ethical, and legal requirements. All patients will provide written informed consent. Results will be monitored by an independent Data Safety Monitoring Board. An independent medical monitor will ensure required activities are performed according to standard operating procedures and direct the co-ordinating team on conduct and reporting. The study is registered on clinicaltrials.gov (NCT05799755; date of registration: 05/04/2023). Results will be published in a peer-reviewed publication.

### Randomisation and drug dispensing

Randomisation and dispensing of trial drugs will be coordinated through a central pharmacy. Once a patient passes screening, the central pharmacy will complete the randomisation form and trial drugs will be shipped directly to the patient’s home. In the case of early discontinuation, any remaining drug will be shipped back to the central pharmacy.

### Visits and measurements

Most study visits will be completed remotely (Fig. 2). Physician and trial co-ordinator visits will be conducted via telemedicine. Patients will be provided with various monitoring devices: blood pressure and heart rate monitor, home spirometer, pulse oximeter, and physical activity monitor wristwatch. Patients will receive training on how to use these devices, including home spirometry training from a PFT technician via telemedicine during screening. Patients will complete patient-reported outcome questionnaires on tablets.

Two types of home spirometry will be conducted. Twice a week, patients will perform home spirometry guided by an avatar on a tablet, but not supervised by a PFT technician. In addition, at baseline and every 4 weeks thereafter, patients will perform home spirometry guided by a PFT technician via telemedicine. Spirometry measurements will be performed according to American Thoracic Society/European Respiratory Society guidelines [29]; patients will be asked to repeat the spirometry if these requirements are not met.

For patients recruited via the decentralised approach, clinic PFTs and HRCT will be performed at a centre near the patient’s home. Patients recruited via a local site will have clinic PFTs and HRCT at the local site or at another centre near their home. After screening, clinic PFTs will be performed at weeks 12 and 24, and an HRCT will be completed at week 24.

For patients recruited via the decentralised approach, blood draws will be made by a research nurse during home visits or at a centre near the patient’s home. Patients recruited via a local site will have blood draws at the local site or at another centre near their home.

### Patients

Eligible patients will be aged ≥ 18 years, with a diagnosis of myositis based on the 2017 European League Against Rheumatism/American College of Rheumatology classification criteria [1] or the presence of myositis autoantibodies (Additional file 2), fibrosing ILD (reticular changes, traction bronchiectasis and/or honeycombing) on an HRCT scan taken within the prior 12 months, and an FVC > 40– ≤ 80% predicted. Patients must meet ≥ 1 of the following criteria for ILD progression at any time within the prior 24 months: relative decline in FVC ≥ 10% predicted; relative decline in FVC ≥ 5– < 10% predicted with worsened dyspnoea; relative decline in FVC ≥ 5– < 10% predicted with worsened fibrosis on HRCT; worsened dyspnoea and worsened fibrosis on HRCT. Patients must be taking 1 or 2 standard of care therapies (glucocorticoid and/or other immunosuppressant listed in Additional file 2) at a stable dose. For patients taking 2 therapies, ≥ 1 must be a non-glucocorticoid. Patients who have taken immunosuppressants other than those listed in Additional file 2 will be considered for eligibility after undergoing a drug washout period. Tapering of the dose of glucocorticoids will be permitted from weeks 4 to 20. An increase in the dose of glucocorticoids is allowed as a rescue therapy once during the trial. No change in non-glucocorticoid immunosuppressants will be permitted. A full list of inclusion and exclusion criteria is provided in Additional file 2.

### Endpoints

Patients will complete the L-PF questionnaire [30] at baseline and then every 4 weeks. This questionnaire, which was developed in patients with pulmonary fibrosis [31], includes a symptoms module (23 questions with recall of the past 24 h) and an impacts module (21 questions with recall of the past week). The symptoms module includes three domains: dyspnoea, cough, fatigue. The primary endpoint in MINT is the change in L-PF questionnaire dyspnoea domain score at week 12.

Key secondary endpoints include the change in L-PF questionnaire dyspnoea domain score at week 24; changes in L-PF questionnaire cough domain, fatigue domain, impacts, and total scores at weeks 12 and 24; the proportion of patients with an increase in dose or change in glucocorticoid/immunosuppressive agent at weeks 12 and 24; and changes in lung function based on clinic PFTs at weeks 12 and 24 (Additional file 2). Safety and tolerability will be evaluated through assessment of adverse events and the proportion of patients who discontinue trial medication.

The rates of patient recruitment, enrolment, screen failure, and drop-out at the local sites and decentralised site will be evaluated. Data collected using remote and clinic enrolment will be compared. The measurement properties of home spirometry versus clinic spirometry will be assessed. Other secondary and exploratory endpoints, including changes in physical activity, steroid use, semi-quantitative and quantitative HRCT scores, pulse oximetry, patient-reported outcomes, and progression-free survival are shown in Additional file 2.

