### Sample size

It is planned that 134 patients with progressive MA-ILD will be randomised. In the INBUILD trial in patients with progressive pulmonary fibrosis, the mean (SD) change (increase) from baseline in the L-PF questionnaire dyspnoea domain score at week 12 was 0.59 (13.44) in the nintedanib group and 1.45 (13.04) in the placebo group. Assuming that 134 patients are enrolled in MINT and the drop-out rate is 20%, 108 patients (54 in each treatment group) will have complete follow-up data at week 12. With 108 patients, and assuming a standard deviation of 13.44, the width of a 2-sided 95% confidence interval for the between-group difference in the change in L-PF questionnaire dyspnoea domain score at week 12 in MINT is 2.54, which is considered appropriate for an exploratory study.

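### The primary dyspnoea score rests on one 24-hour reading at each end; averaging a few tablet readings is a cheap way to narrow its interval, not the repair of an error

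*Protocol article*

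**What the plan says.** All references are to the protocol article.

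- **Endpoints.** The questionnaire "includes a symptoms module (23 questions with recall of the past 24 h", and dyspnoea is one of that module's three domains. On timing: "Patients will complete the L-PF questionnaire [30] at baseline and then every 4 weeks". On the outcome: "The primary endpoint in MINT is the change in L-PF questionnaire dyspnoea domain score at week 12". No repeat completion around a time point and no averaging is described.
- **Visits and measurements.** "Patients will complete patient-reported outcome questionnaires on tablets". Most visits are remote. A tablet is already in frequent use at home: "Twice a week, patients will perform home spirometry guided by an avatar on a tablet, but not supervised by a PFT technician". That the questionnaires are answered on the same tablet at home is an inference, though a natural one.
- **Sample size.** The INBUILD change in this score at week 12 "was 0.59 (13.44) in the nintedanib group and 1.45 (13.04) in the placebo group" (mean, SD). "With 108 patients, and assuming a standard deviation of 13.44", the article gives a 95% interval width of 2.54, "which is considered appropriate for an exploratory study". No power or target difference is stated, so precision is the whole case for 134 patients.

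**The concern.** Breathlessness varies from day to day. A score that looks back 24 hours and is taken once at each end carries that variation twice in the change: once from the baseline day and once from the week-12 day. The variation says nothing about treatment, yet it adds to the SD of the change and so to the width of the interval.

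Two features make this worth raising here. Precision of this one difference is the only stated basis for the sample size. And the trial is built for frequent remote measurement: Table 1 counts more frequent measurement among the advantages of decentralised trials. The trial uses that advantage for spirometry but, as described, not for its primary endpoint. At stake is precision that could be had without more patients, visits or staff.

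**Working it through.** **1. The article's own figure.** Inputs from Sample size: SD 13.44, 108 completers, 54 per arm, two-sided 95%.

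- Completers: 134 × 0.8 = 107.2, stated as 108.
- Two-arm half-width: 1.96 × 13.44 × √(2/54) = 5.07. Full width: 10.14.
- The stated 2.54 is not reproduced. The nearest match is the half-width for a single group of 108: 1.96 × 13.44 / √108 = 2.53. That is not an interval for a difference between two arms.

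The starting point below is therefore 5.07, not 2.54.

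**2. Effect of averaging.** Let f be the share of the change variance that is independent day-to-day noise, split equally between the two ends. The documents do not give f, so it is an assumption shown over a range. Averaging m days at both ends multiplies the change variance by 1 − f(1 − 1/m), which for m = 3 is 1 − 2f/3. Averaging only the week-12 end gives 1 − f/3. The half-width is 5.07 × √ratio.

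| f (assumed) | Ratio, both ends | Half-width, both ends | Equivalent completers (108/ratio) | Half-width, week 12 only |
|---|---|---|---|---|
| 0 | 1.000 | 5.07 | 108 | 5.07 |
| 0.1 | 0.933 | 4.90 | 116 | 4.98 |
| 0.2 | 0.867 | 4.72 | 125 | 4.90 |
| 0.4 | 0.733 | 4.34 | 147 | 4.72 |
| 0.6 | 0.600 | 3.93 | 180 | 4.53 |

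**3. Correlated neighbouring days.** If daily noise has correlation r between days in the same week, the both-ends ratio becomes 1 − (2/3)f(1 − r). With f = 0.4 and r = 0.5 (both assumed) it is 0.867, so the half-width is 4.72 rather than 4.34. The table is the best case for each f.

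**4. Can averaging restore 2.54?** No. Even at f = 1 the three-day ratio is 1/3, and 5.07 × √(1/3) = 2.93.

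**5. Mean of weeks 8 and 12 minus baseline.** With equal variances and equal correlations across visits (assumed), the variance ratio is 1.5/2 = 0.75 and the half-width is 5.07 × √0.75 = 4.39. This needs no new data but answers a different question. If, for illustration, half of the week-12 effect were present at week 8, the mean would capture (0.5 + 1)/2 = 75% of it, while the half-width falls only to √0.75 = 87%.

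**6. Scale.** The INBUILD difference at week 12 was 1.45 − 0.59 = 0.86. Every half-width above is several times that.

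**The case against.** The strongest objection is that nothing is wrong. The questionnaire is used with its own recall period on a regular schedule, and the Discussion says that the score captures changes meaningful to patients. That stands: this is an efficiency suggestion.

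A reader might go further and infer that single-day noise makes the interval wider than the sponsor planned. The documents do not support that. The 13.44 is the observed SD of the same change at the same week in INBUILD. If INBUILD also used single completions, which the article does not say, the noise is already in the planning figure.

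The gain is unknown. With no day-to-day or test-retest figure in the documents it may be nil, and correlated days reduce it. That stands, which is why the range starts at zero.

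A condensed article may leave completion windows, baseline adjustment and repeated-measures modelling to the full protocol or SAP. The Analyses section does refer to an undefined time-frame for each endpoint. So one cannot say that week-8 data go unused in the analysis, only that they are not part of the endpoint as defined. The Endpoints section is nevertheless explicit about schedule and endpoint, and neither suggests averaging.

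Finally, Table 1 itself warns that participants may feel overburdened by home devices, and the trial is exploratory with descriptive analysis only. Both points limit the weight of the suggestion. Neither removes it, because four short completions are little beside twice-weekly spirometry, and the interval is still the only stated rationale for size.

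**Conclusion.** This holds as a cheap improvement, not as an error or contradiction. As described, the primary endpoint is the change between two single 24-hour readings, and its interval is wider than it need be. It is not shown to be wider than planned.

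Three-day averaging at both ends would take the half-width from 5.07 to somewhere between 5.07 (f = 0) and 3.93 (f = 0.6). This assumes SD 13.44, 54 per arm, independent daily noise, and INBUILD readings that were themselves single completions. Even the best of these figures would not resolve a difference as small as the 0.86 seen in INBUILD. The benefit is a tighter descriptive estimate.

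The stated width of 2.54 is a separate matter. It does not follow from the article's inputs and must be restated as a half-width of 5.07 (full width 10.14), whether or not the schedule changes. It should not be read as a result of single-day measurement or as something that averaging could deliver.

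**What to change.** Amend the Endpoints section as follows.

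1. Patients complete the dyspnoea domain on the tablet on 3 separate days in the 7 days up to baseline, and on 3 separate days in the 7 days up to week 12, all before open-label treatment begins. The primary endpoint is the change between the two averages, using the available days if one is missed.
2. For patients already past baseline, average only the week-12 days. The rule is the same in both arms, and randomisation balances these patients, so it does not bias the comparison.
3. Keep the single-day change as a sensitivity analysis, for comparison with INBUILD.
4. Report the mean of weeks 8 and 12 minus baseline as supportive only, noting that it dilutes an effect still developing at week 8.
5. Correct the width in the Sample size section separately.

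Cost: a small amendment and tablet scheduling, with no added visits, staff or patients. Each patient makes four extra short completions (six instead of two). The sponsor should check that the domain may be given apart from the rest of the symptoms module; if not, each extra completion is the full 23 questions. Comparability with INBUILD is slightly looser, and baseline precision is mixed across patients if the change is made mid-trial. If the sponsor keeps single-day readings, a sentence saying why would be enough.
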